#### Analysis of secondary outcomes.

Secondary outcomes, including BDI-II, HAMA, SCARED, C-SSRS, PSQI, PedsQL 4.0, CGI-S, CGI-I, and RRS, will be analyzed according to outcome type. Repeated continuous outcomes will primarily be analyzed using linear mixed-effects models, where appropriate, with treatment group, time, and treatment-by-time interaction included as fixed effects and the corresponding baseline value included as a covariate. CGI-I will be analyzed as a post-baseline global improvement rating. Ordinal or categorical outcomes will be analyzed using appropriate generalized linear models, generalized estimating equations, ordinal regression models, or non-parametric methods, depending on the distribution and scale properties of the data. Results will be summarized at each prespecified assessment time point together with effect estimates and 95% confidence intervals where appropriate.

#### Analysis of exploratory outcomes.

Exploratory outcomes, including MRI-derived functional connectivity, THINC-it performance, EEG measures, eye-tracking measures, fNIRS measures, facial expression features, and acoustic features, will be analyzed using descriptive and exploratory approaches. For continuous exploratory measures, changes from baseline and between-group differences over time will be estimated using mixed-effects models or other suitable multivariable methods, where appropriate, depending on the structure and dimensionality of the data. Neuroimaging analyses will use seed-based or whole-brain approaches to characterize changes in depression-relevant circuits. Because of the pilot nature of the study and the large number of exploratory measures, these analyses will be regarded as hypothesis-generating.

### Missing data and sensitivity analyses

Patterns of missing data will be examined descriptively. For repeated continuous outcomes, mixed-effects models will serve as the primary analytic approach under the assumption that data are missing at random. Sensitivity analyses will be conducted, where appropriate, using multiple imputation, complete-case analysis, and alternative assumptions regarding missing data to assess the robustness of the findings. Additional sensitivity analyses may also be performed to examine the potential influence of protocol deviations or extreme values.

Exploratory subgroup analyses may be conducted, if data permit, according to selected baseline characteristics such as age, sex, and baseline depression severity. Given the small sample size, these analyses will be interpreted cautiously and considered hypothesis-generating.

### Safety analysis

Safety outcomes will be summarized descriptively by treatment group, including the type, frequency, severity, and incidence of adverse events and serious adverse events. Between-group comparisons will be conducted using the chi-square test or Fisher’s exact test, as appropriate. Tolerability-related indicators, including treatment interruption, dose reduction, or discontinuation, will also be summarized descriptively.

## Ethics and dissemination

### Ethical considerations

This investigator-initiated study at the First Affiliated Hospital of Chongqing Medical University is a randomized, double-blind, three-arm, sham-controlled, parallel-group pilot clinical trial. All study procedures will be conducted in accordance with the ethical standards of the relevant national and institutional committees on human experimentation and with the Declaration of Helsinki (1975), as revised in 2013. The study protocol was approved by the Ethics Committee of the First Affiliated Hospital of Chongqing Medical University on 21 August 2025 (Ethical Approval No. 2025-533-01), and the trial was registered at ClinicalTrials.gov on 15 September 2025 (Registration No. NCT07185438). The trial protocol and statistical analysis plan are publicly available through the trial registration record. Participant recruitment commenced on 1 September 2025 and is expected to be completed on 31 December 2026. Any protocol modifications, including changes to study procedures or participant safety measures, will be documented as protocol amendments and communicated in a timely manner to the Ethics Committee and relevant investigators. All amendments will be reviewed and approved by the Ethics Committee before implementation to ensure ongoing compliance with ethical standards.

Written informed consent will be obtained before enrolment. Because all participants are adolescents, the principal investigator will ensure that written informed consent is obtained from participants’ legal guardians and that assent or consent from participants is obtained in accordance with applicable ethical and legal requirements. Before consent is obtained, participants and their guardians will receive a clear explanation of the study procedures, potential risks, and anticipated benefits, and they will have the opportunity to ask questions.

Participants will be reimbursed for study-related examination costs incurred during the trial, and all required study equipment will be provided at no cost. Upon completion of study participation, participants will receive compensation for transportation expenses related to trial visits. In the event of any trial-related adverse events, necessary medical expenses will be covered and additional compensation will be provided in accordance with institutional policies and applicable regulations.

All personal information relating to potential and enrolled participants will be collected, stored, and shared in strict compliance with applicable privacy and data protection regulations. Appropriate safeguards will be implemented to protect confidentiality throughout the study, including secure data storage and access controls that restrict identifiable information to authorized study personnel only.

### Monitoring

A Data Monitoring Committee (DMC) will be established and will comprise experts in clinical research, biostatistics, and relevant clinical specialties from the First Affiliated Hospital of Chongqing Medical University. The primary responsibilities of the DMC are to oversee participant safety, review trial conduct and progress, and monitor data quality and integrity. The committee will review study progress at regular intervals throughout the trial.

At prespecified time points, the Principal Investigator and the DMC will review accumulating trial data, with particular attention to safety outcomes, study feasibility, and preliminary clinical signals. In the event of serious adverse events, major safety concerns, or other circumstances that may affect the ethical or scientific conduct of the study, the Principal Investigator and the DMC may recommend modification, temporary suspension, or early termination of the trial. Access to interim data will be restricted to DMC members, the Principal Investigator, and designated study personnel with authorization to review such data.

In addition, routine monitoring will be conducted by the Ethics Committee of the First Affiliated Hospital of Chongqing Medical University to ensure adherence to the protocol, protection of participants’ rights and welfare, and compliance with applicable regulatory requirements. Monitoring activities may include on-site visits, source data verification, and ongoing review of safety-related information.

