### Randomization

Randomisation will be conducted before the first treatment session [24]. Participants will be assigned in a 1:1:1 ratio to the rs-fcMRI-guided rTMS group, the conventional left DLPFC-targeted rTMS group, or the sham rTMS group [25,26]. The allocation sequence will be generated by an independent statistician who is not involved in participant recruitment, intervention delivery, or outcome assessment, using a computer-generated permuted block randomisation scheme with a block size of 9.

Allocation concealment will be ensured using sequentially numbered, sealed, opaque envelopes, which will be opened immediately before the first treatment session. The assigned study number will determine treatment allocation throughout the trial. rTMS will be delivered by certified operators who, because of the nature of the intervention, will not be blinded to treatment condition; however, they will not be involved in recruitment, clinical evaluation, or outcome assessment.

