### Blinding

Participants, treating clinicians responsible for routine clinical care, and outcome assessors will remain blinded to treatment allocation throughout the trial [27]. Any instance of inadvertent unblinding of an outcome assessor will be documented in detail, and all subsequent assessments for that participant will be conducted by an alternative blinded assessor. After completion of the intervention, outcome assessors will be asked to guess participants’ group assignment in order to evaluate the integrity of blinding.

Personnel involved in treatment delivery, including unblinded staff and certified rTMS operators, will be strictly excluded from recruitment, clinical evaluation, outcome assessment, and data analysis to minimize the risk of bias.

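### Interim clinical data are open to the principal investigator and undefined study personnel, with no limit to pooled data and no separation from recruitment, care or outcome assessment

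*Protocol article*

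**What the plan says.** The Monitoring section of the protocol article fixes three things.

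- **Content of the review.** At times set in advance, "the Principal Investigator and the DMC will review accumulating trial data, with particular attention to safety outcomes, study feasibility, and preliminary clinical signals".
- **Access.** "Access to interim data will be restricted to DMC members, the Principal Investigator, and designated study personnel with authorization to review such data".
- **Action.** After serious adverse events, major safety concerns or other matters touching the ethical or scientific conduct of the study, "the Principal Investigator and the DMC may recommend modification, temporary suspension, or early termination of the trial".

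The DMC is to "comprise experts in clinical research, biostatistics, and relevant clinical specialties from the First Affiliated Hospital of Chongqing Medical University". No member from outside that hospital is mentioned.

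The Blinding section gives the masking claim: "Participants, treating clinicians responsible for routine clinical care, and outcome assessors will remain blinded to treatment allocation throughout the trial". It adds that personnel who deliver treatment, and so know the allocation, "will be strictly excluded from recruitment, clinical evaluation, outcome assessment, and data analysis to minimize the risk of bias". The Randomization section likewise keeps the operators away from recruiting, evaluating and assessing participants.

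**The concern.** The article recognises that people who know the allocation should not recruit, evaluate or assess, and it applies this to the treatment staff. It applies no such rule to people who see interim outcome data. That group includes the principal investigator and a category of staff whose roles are not described.

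At stake is the conduct of the trial. Someone who knows how the arms are separating may, without intending to, change who is approached, how a participant's course is handled, or which changes to the trial are put forward. The trial is called double-blind and runs at one centre, so the people who run it work closely together. CDRS-R response and remission are among its primary outcomes, and their value for planning the next trial depends on conduct that is not steered by an early trend.

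**Working it through.** The plan gives no figure to reproduce: the sample size is pragmatic, and there is no interim boundary, alpha or power. The check compares what each group may know with what it is barred from doing.

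| Group | What it may know | Stated bar from recruitment, evaluation or assessment |
|---|---|---|
| Treatment-delivery staff and operators | Allocation | Yes, in Randomization and Blinding; Blinding also bars them from data analysis |
| Treating clinicians, outcome assessors | Declared blinded to allocation | Not needed if blinded, but nothing says they cannot be designated to see interim data |
| DMC members | Interim data | None stated |
| Principal investigator | Interim data, with joint review and joint recommendation | None stated; not listed among the blinded roles |
| Designated study personnel | Interim data | None stated; roles not defined |

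**Are the interim data by arm?** The Monitoring section does not say. Two other places make a by-arm reading natural. The Discussion uses the same term for a comparison of guided with standard left DLPFC stimulation, and the Sample size section lists preliminary efficacy signals among the things the trial should estimate. Neither describes an interim report. What the documents support is that access is not limited to pooled data.

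**Where could knowledge of a trend act?** Recruitment was planned to run from September 2025 to December 2026, so any review in that period falls while participants are still being enrolled. Medication may be changed where clinically indicated (Interventions; Concomitant medication management), and a treating clinician's judgement can end the intervention (Discontinuation of the intervention). Treating clinicians are declared blinded, but no sentence keeps them, recruiters or assessors out of the designated group.

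**How visible would a trend be?** There are 45 / 3 = 15 participants per arm. At full size, one responder moves an arm's response rate by 1 / 15 = 6.7 percentage points, and with fewer participants by more. A by-arm interim table could therefore show a marked difference that rests on very few people. This shows how easily an unstable trend could appear; it does not measure bias.

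**The case against.** The strongest reply has four parts.

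1. **No contradiction with the blinding statement.** The principal investigator is not among the roles declared blinded, and by-arm summaries alone would not tell an assessor what an individual received. This stands. A reader might infer that the masking is breached, but the documents show only that it is not protected on this side.
2. **No stopping on efficacy.** A reader might infer that the trial can be stopped on interim efficacy, or that study staff can recommend this. The named triggers are serious adverse events and major safety concerns, followed by an open-ended clause; efficacy is not named. Designated personnel have access but no recommending role, and amendments need Ethics Committee approval before use. This also stands.
3. **Consent is oversight.** The article says "the principal investigator will ensure that written informed consent is obtained from participants’ legal guardians". That does not show that the principal investigator personally selects or approaches patients. This stands too.
4. **A pilot, and a charter may exist.** The trial estimates rather than tests, so interim looks inflate no confirmatory error rate, and open and closed reports are usually set out in a charter. The first half limits the consequence but leaves bias in conduct untouched. The second half fails: the article does not leave access open, it grants it. A charter that kept interim clinical data from the principal investigator would conflict with the published text.

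A reader might also infer that interim arm counts reveal coming assignments, because the sequence uses a "computer-generated permuted block randomisation scheme with a block size of 9". Prediction of that kind needs knowledge of each allocation as it happens. The Monitoring section describes periodic review and does not say that arm counts are shown, so this inference is not supported.

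**Conclusion.** The point holds as a missing firewall. The article gives the principal investigator and undefined study personnel access to interim data that include clinical signals. It does not limit them to pooled data, and it does not separate them from the roles that its own Randomization and Blinding sections protect. Harm depends on two conditions that the documents leave open: that the data are shown by arm, and that someone who sees them recruits, treats, assesses or shapes changes to the trial. The size of any bias cannot be calculated from the documents. For an estimation pilot the consequence is moderate, but the text should be corrected because the remedy is specific and cheap.

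**What to change.** Amend the Monitoring section to say that:

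- by-arm interim data go only to DMC members and to an independent statistician who prepares the closed report;
- the principal investigator and study personnel receive only pooled safety, recruitment and data-quality summaries;
- anyone with by-arm access takes no part in recruitment, routine care or outcome assessment;
- the DMC passes on its recommendations without by-arm results.

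The cost is small: an amendment with Ethics Committee approval, matching text in any DMC charter, and two reports per review in place of one. The independent statistician who generates the allocation sequence is already outside recruitment, treatment delivery and outcome assessment and could prepare the closed report, so no extra post need follow. Recruitment is under way, so the change should be in place before the next data review.

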### Dissemination

All participants and their guardians, where appropriate, will be provided with a summary of the study results. Findings will be published in peer-reviewed journals and disseminated to academic, professional, and public audiences through conferences and other appropriate communication channels, including social media where suitable.

### Patient and public involvement

Patients or the public will not be involved in the design, or conduct, or reporting, or dissemination plans of our research.

## Discussion

This study is a randomized, double-blind, three-arm, sham-controlled, parallel-group pilot trial designed to evaluate the feasibility, safety, and preliminary clinical efficacy of rs-fcMRI-guided rTMS targeting a circuit-informed DLPFC-sgACC axis in adolescents with MDD [33,34]. By directly comparing rs-fcMRI-guided individualized targeting with conventional left DLPFC stimulation and sham stimulation, the trial aims to clarify whether this imaging-guided neuromodulation approach can be delivered reliably in adolescents while also generating early clinical signals.

Although rTMS is an established treatment for adult depression and is generally associated with good tolerability and mostly mild, transient adverse effects [35], evidence in adolescent MDD remains limited and inconsistent. Existing studies differ substantially in design, stimulation targets, treatment parameters, and participant characteristics, which may partly explain the heterogeneity of reported findings. Moreover, the practical feasibility of delivering repeated rTMS sessions together with MRI and multimodal assessments in adolescents has not been adequately characterized. These uncertainties support the need for a pilot trial that addresses both clinical promise and real-world implementation.

The rationale for rs-fcMRI-guided targeting is grounded in adult neuroimaging evidence suggesting that antidepressant response to rTMS may be greater when stimulation is delivered to left DLPFC sites showing the strongest negative functional connectivity with the sgACC, a key node within depression-related neural circuits [36]. Compared with conventional targeting methods, this approach may allow more precise modulation of fronto-limbic networks involved in mood regulation. Accordingly, the present study will explore whether individualized rs-fcMRI-guided stimulation of the DLPFC-sgACC circuit is associated with more favorable preliminary clinical signals than standard left DLPFC stimulation in adolescents with MDD. It will also examine whether symptom improvement is accompanied by modulation of DLPFC-sgACC connectivity and broader changes in depression-relevant networks.

The principal value of this pilot trial lies in its ability to inform the next stage of clinical development. Feasibility and safety outcomes, including recruitment feasibility, intervention adherence, retention at the 6-month follow-up, and adverse event monitoring, will help determine whether protocol modifications are needed before a larger trial is undertaken. Additional trial process indicators, such as assessment completion, exploratory multimodal data completeness, tolerability-related findings, and blinding integrity, will further inform the feasibility of implementing the protocol in future studies. At the same time, preliminary clinical and circuit-level findings may guide the selection of outcome measures, follow-up schedules, and biomarker acquisition procedures for subsequent trials. Although this study is not designed to establish efficacy definitively or to develop predictive models, it may provide an initial empirical basis for more personalized rTMS strategies in adolescent depression and support the future standardization of individualized neuromodulation approaches in youth populations.
